## Intervention

### Intervention and control groups

In addition to the usual care, the participants of the intervention group will receive the educational, supportive mobile application-based intervention (Additional file 2). The participants will have these applications for 6 months and the aforementioned measurements will be registered in it. Reminders for dose and time of drug intake, date of clinical visit, and other reminders will be activated. The users will be provided with the scientific information and skills required to identify the disease and its methods of control by the mobile application.

The participants in the comparison arm will receive the usual standard care based on the Joint National Committee (JNC) guideline. The usual care includes, measuring the patient’s BP, necessary assessments based on the patient’s history and circumstances, the specialist physician’s judgment, medication prescription, and other medical measures. The number of appointments and assessments in each group will be the same. The intervention and control participants’ appointment days will differ and the members of one group will not be in touch with those of the other.

The BPMAP application contains educational content that is meant to raise the level of knowledge in hypertensive patients regarding its complications and methods of control. Moreover, it contains supportive measures such as important reminders for time of drug use, smoking cessation, and weight loss.

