### Intervention delivery

The software will be installed on the mobile phone and its operation will be taught individually. The patients will work with the application in the presence of the research team, and any existing problems will be resolved. Since BP measurement will take place at the individual’s home and with a personal sphygmomanometer, the patients’ personal sphygmomanometers will be calibrated at the same time that the application is installed. In case there is a large difference in readings, or if the sphygmomanometer is faulty, the patient will be advised to change it. The strategies foreseen for adherence improvement include reminders set at defined intervals in the form of pop-up messages. In order to monitor adherence, the data collected on the server will be used.

In addition to the application, a server has been designed in which the users’ activities will be collected. Items such as the duration the application has been left open by the user, the sections used by the user (in addition to registering their time and duration), and BP registration, etc. will be registered. Every time the user’s mobile is connected to the Internet, the data will be uploaded and saved on to the server. These data can be used as a proxy of adherence to the intervention.

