#### Regular BP monitoring

BP can be regularly monitored by regularly measuring and saving the relevant data in the mobile app. For every timely registration a score will be awarded. This part of the study is 60 days long. The participants will be asked to measure and register their BP once every other day. A score of 25 and higher will be considered appropriate.

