### Follow-up

The participants will be examined seven times at 2-week intervals (Table 1). In the first visit, after ensuring the participant’s inclination to participate in the study and after the informed consent form is completed, the baseline data questionnaire will be completed by the researcher. Clinical measurements, such as systolic and diastolic BP, waist circumference and hip circumference, BMI, and biochemical measurements, such as LDL, HDL, and total cholesterol levels, will be performed.

**Table 1 Tab1:** Steps taken in each visit

	Study period										
	Enrollment	Allocation	Post allocation								Close-out
Week	−1 to 0	0 ± 2 days	2 ± 2 days	4 ± 2 days	6 ± 2 days	8 ± 2 days					24 ± 2 days
Time point	1^st^ visit	2^nd^ visit	3^rd^ visit	4^th^ visit	5^th^ visit	6^th^ visit					7^th^ visit
Enrollment:	×										
Eligibility screen	×										
Informed consent	×										
Allocation	×										
Intervention		×	×	×	×	×	×	×	×	×	×
Assessment	×					×					×
Baseline variables	×					×					×
Measuring adherence to treatment	×					×					×
Measuring adherence to the diet	×					×					×
Evaluating the predisposing, enabling, and reinforcing factors of adherence	×					×					×
Measurement of systolic and diastolic BP, waist circumference, and BMI	×	×	×	×	×	×	×	×	×	×	×
Evaluating the regular monitoring of BP by the mobile application	×	×	×	×	×	×	×	×	×	×	×
Evaluating the usability of the software						×					×
Evaluating the level of satisfaction of the software/application						×					×

*BMI* Body Mass Index, *BP* blood pressure

The 2nd visit will be made a week after the first. The application will be installed on the cell phones of the intervention group’s patients and its operation will be taught to them. Any problems that arise will be dealt with accordingly. Moreover, the sphygmomanometer used by the patient at home will be evaluated for its precision and sensitivity (calibration). In order to ensure that the patients measure their BP correctly at home, the methods applied by them will be controlled, and if faulty, corrected. Clinical measurements and usual care will be performed. The usual care includes history taking, BP measurement, and diagnostic and therapeutic measures based on the JNC guideline on high blood pressure.

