### Withdrawal criteria

The participant will be excluded from the study if any of the following are seen during the study:Lack of registration of data in the application for more than a weekLack of interest in continuing to participate in the studyNonattendance for two consecutive visitsChange in dose and type of antihypertensive medicationHospital admission due to CVDEmigration from TehranDeath

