## Statistical methods

The qualitative findings of the study will be described using frequency and percentage frequency, and the quantitative findings will be described using mean and standard deviation. To analyze the effectiveness of the main outcome variable of the study, we will use analysis of covariance (comparison of mean changes in score of the adjusted questionnaire – based on the baseline score at the beginning of the study and other possible confounding factors) at a confidence interval of 95 %. This approach will be repeated for all the quantitative variables.

The remaining qualitative variables of the study will be compared by the chi-squared test between the two groups. The main approach of the study will be intention-to-treat. The final results will be analyzed per protocol. Lost data will be replaced through multiple imputation techniques.

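### Excluding patients from the study for not registering in the app can act only in the app arm, so the stated intention-to-treat analysis cannot be delivered as written

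*Protocol article*

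**What the plan says.** **Withdrawal criteria** (Protocol article). "The participant will be excluded from the study if any of the following are seen during the study": the first item on the list is going longer than seven days without entering data in the app. The consequence is exclusion from the study, not merely being counted as a non-user.

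**Who has the app.** Under Intervention and control groups, "the participants of the intervention group will receive the educational, supportive mobile application-based intervention", in addition to usual care. Under Follow-up, "The application will be installed on the cell phones of the intervention group’s patients", at the second visit. For the other arm, "The participants in the comparison arm will receive the usual standard care based on the Joint National Committee (JNC) guideline"; no app is mentioned.

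**What app activity means.** Under Intervention delivery, "In order to monitor adherence, the data collected on the server will be used", and the same section accepts server data as a stand-in for adherence to the intervention.

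**Analysis.** Statistical methods states: "The main approach of the study will be intention-to-treat". The next sentence assigns the final results to a per-protocol analysis. The section then ends: "Lost data will be replaced through multiple imputation techniques". It names no imputation model.

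**Assessments.** Table 1 schedules treatment adherence at baseline, week 8 and week 24. Nothing in the article provides for assessing a participant after exclusion.

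**The concern.** An intention-to-treat comparison needs outcomes from all randomised patients, whatever they did with the intervention. Here the plan itself removes patients because they did not use the intervention, and does so in one arm only. Patients in the control arm who would have behaved in the same way stay in.

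The removed patients may well be reachable, so the missing outcomes are created by the rule. The outcome on which the trial is sized is a treatment-compliance score. People who stop registering in an adherence app are plausibly poorer adherers, or benefit less from the app. If so, the remaining app arm looks better than the randomised app arm. The Discussion part of the abstract envisages possible use in a national hypertension control plan, where non-users would count.

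**Working it through.** **1. The plan's own figure.** Sample size inputs: means 40 and 45, SD 10, two-sided 5%, power 80%. Per arm: 2 × (1.960 + 0.842)² × 10² / 5² = 62.8, so 63 (64 with a t-test), against the stated 60. At 60 per arm, power is 78.2%. The total of 132 is 120 × 1.10. This small shortfall is a separate matter. What is used below is the 5-point difference, the SD of 10, 66 per arm, and the 10% allowance for losses of all kinds.

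**2. What the estimate becomes.** Let p be the share of the app arm excluded for non-registration (not given, so assumed), E_u the app effect in those who keep registering, and E_n the effect in those who do not.

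- Intention-to-treat effect = (1 − p) × E_u + p × E_n
- Effect from retained patients = E_u, if non-users would otherwise score the same
- Overstatement = p × (E_u − E_n)
- If non-users also score d points lower whether or not they have the app, add p × d

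With E_u = 5 and d = 0:

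| p | True effect, E_n = 0 | Overstatement | True effect, E_n = 2.5 | Overstatement | Overstatement, E_n = 5 |
|---|---|---|---|---|---|
| 10% | 4.5 | 0.5 (11%) | 4.75 | 0.25 | 0 |
| 20% | 4.0 | 1.0 (25%) | 4.50 | 0.50 | 0 |
| 30% | 3.5 | 1.5 (43%) | 4.25 | 0.75 | 0 |

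**3. Does imputation repair it?** This was simulated with 66 per arm, SD 10, an assumed baseline-to-final correlation of 0.5, covariance analysis, 20 imputations from arm and baseline, 1,000 trials and no other loss.

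| Setting | All patients observed | Excluded, then imputed | Excluded and dropped |
|---|---|---|---|
| p = 10%, E_n = 0 | 4.56 | 5.05 | 5.05 |
| p = 20%, E_n = 0 | 3.89 | 4.89 | 4.89 |
| p = 30%, E_n = 0 | 3.52 | 5.04 | 5.03 |
| p = 20%, E_n = 5 | 5.05 | 5.06 | 5.05 |

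The gaps between the first two columns (0.49, 1.00, 1.52, and about 0) match the algebra. Under this model, imputing and dropping are the same analysis in practice. Leaving arm out of the imputation model reduces the overstatement but does not remove it (4.39 against 3.93 at p = 20%, E_n = 0).

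**4. No app effect at all.** If the app does nothing and non-users score 5 points lower in any case, p = 20% gives a spurious 1.0 point and a 10% rejection rate. With p = 30% these are 1.5 points and 13%, against a nominal 5%. The 5-point deficit is an assumption.

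**5. Could p be material?** Entries are requested every other day, so 60 days hold 30 entries. Suppose entries are missed independently, 20% of the time. Over 60 days, exclusion after four misses in a row affects 3%; after three in a row (eight days between entries) it affects 17%. With 30% missed, the figures are 15% and 44%. The rate therefore depends heavily on habits and on how the rule is read, and it can exceed the 10% allowance. Also, assuming one point per entry, a patient who misses four in a row but no others scores 26. That passes the article's own threshold of 25 for regular monitoring, yet the patient could be excluded.

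**The case against.** **No imputation model is stated.** A reader might infer that the plan fills in excluded patients from those who kept using the app. The text does not say so. The model may sit in an analysis plan not shown, and a different model could reduce the bias. The equivalence in step 3 is therefore conditional. What stands is that no model can recover outcomes that the trial stops collecting.

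**The per-protocol sentence points another way.** On that reading the excluded patients are simply dropped. This changes the route, not the result, and leaves the two sentences unreconciled.

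**Not all outcomes are lost.** A patient excluded after week 8 (day 56) has week 8 data, and Table 1 includes treatment adherence at that visit. Those data could inform imputation, and step 3 does not use them. This objection stands and makes the overstatement there an upper illustration for late exclusions.

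**The direction is not guaranteed.** Someone who lapses for eight days after months of use may have benefited fully. If non-users benefit equally and score no lower, there is no bias.

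**An article condenses.** Follow-up after exclusion might be described in a fuller document. But the article states exclusion from the study, which is more than leaving a detail out.

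**Inferences that the documents do not support:**

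- *Patients who follow instructions are excluded soon after day 60.* Of the monitoring task the article says "This part of the study is 60 days long", and the exclusion rule has no end date. But the app is held for six months, measurements are to be registered in it, and Table 1 continues monitoring to close-out. Whether entries are expected after day 60 is unclear.
- *Offline users are excluded by mistake.* Upload needs a connection, but activity is logged with its time, and the rule is not tied to upload time.
- *The other withdrawal criteria inflate the effect in the same way.* They can apply in both arms and could bias in either direction.
- *The rule removes every control.* That is its literal result, but plainly not its intent.

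**Conclusion.** The structural fault holds. A post-randomisation exclusion that only the app arm can meet, based on adherence to the intervention and with no outcome collection afterwards, is incompatible with the intention-to-treat analysis that the article calls its main approach. This rests on reading exclusion from the study as the end of assessments.

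Overstatement of the app effect is the likely direction, because non-use is likely to go with poorer adherence or less benefit. The size is unknown: the article gives neither an exclusion rate nor the effect in non-users. Within the assumed range of 10% to 30% excluded and a 5-point effect in users, it runs from nil (equal benefit, no lower scores) through 0.25 to 0.75 points (2.5-point benefit) to 0.5 to 1.5 points (no benefit). It would be larger if non-users also scored lower regardless of the app, and smaller if week 8 data were used. The documents do not support a single figure for bias or type I error.

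**What to change.** **Withdrawal criteria.** Replace exclusion from the study for app non-registration with wording such as: *recorded as not using the app; week 8 and week 24 assessments continue and are analysed in the allocated arm*. For the other criteria, continue outcome collection where the patient is alive, reachable and still consents. This concerns data collection only and leaves treatment decisions as they are.

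**Statistical methods.** State that the primary analysis is intention-to-treat on all randomised patients, using these observed outcomes, and that the per-protocol analysis is secondary. Limit multiple imputation to outcomes that could not be obtained, and include available week 8 data in the model. A sensitivity analysis under non-random missingness is optional.

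**Cost.** A short amendment and a few sentences of analysis text. Weeks 8 and 24 are already scheduled visits, and the article describes the trial as recruiting. The price is some effort to bring non-users back and a possibly smaller estimated effect. Changing only the imputation model would not be enough, because uncollected outcomes cannot be recovered later.

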## Discussion

The goal of controlling and treating HTN is to prevent complications such as cardiovascular, renal, cerebrovascular and other diseases. Luckily, there are effective treatments for HTN. The JNC HTN treatment management guideline – compiled approximately every 4 years by the American Heart Association – is the basis of the standard treatment of HTN [3]. In addition to adherence to treatment, hypertensive patients need to self-manage their health behaviors such as weight loss, smoking cessation, eating a low-sodium diet, and appropriate exercise – particularly aerobic. However, in spite of the availability of medication patient adherence to regular drug intake has been reported at only 30–50 % [14]. According to the WHO’s 2002 report, drug compliance in the long-term treatments of chronic diseases overall among developed countries is only 50 % [14]. Any of the following reasons may contribute to this noncompliance: treatment of asymptomatic patients, drug side effects, the patient’s disbelief in the effectiveness and benefit of treatment, lack of motivation, insufficient awareness of the individual of the disease and its physical complications, lack of adequate knowledge and practice on the required drug treatment and nutritional diet, miscommunication between the patient and physician, the complexity of treatment, the cost of treatment, insufficient attendance for follow-up on the part of the patient, and the existence of certain psychological problems such as depression [15].

The emergence of smart phones has made its application in various fields possible, including that of medicine. The use of mobile-based technologies in health-related topics is on the rise owing to their easy application, low cost, accessibility unbound by time and place, and overcoming the issue of distance in access to services [16]. Here we will use the BPMAP application to enable, identify and self-manage and optimally control the determinant factors of HTN and overcome the barriers to adherence to treatment. The content of the program has been designed according to the constructs of a behavior-change model, the PRECEDE model. These constructs include: (1) predisposing factors such as knowledge and attitude, (2) enabling factors, which are those factors that prepare the ground for the behavior change, and (3) reinforcing factors, which are those factors that result in the adoption of a different behavior and a rewarding of persistence of that particular behavior change [17, 18].

Among the limitations of this study is the self-report nature of the questionnaire and the need to register the measurements in the application. The necessity of owning a smart phone is another limitation. Some of the strengths of the study are: (1) using the mobile phone as an intervention tool, a technology that is ubiquitous and has no temporal and spatial limitations, (2) safeguarding individuals’ privacy at the time of data delivery and reception of feedback appropriate to the individuals’ data, (3) sampling of both control and intervention groups from the same medical center, and (4) the low cost of the study.

## Trial status

This trial is at the recruitment stage.

## Abbreviations

BMI: Body Mass Index
BP: Blood pressure
BPMAP: Blood Pressure Management Application
CVD: Cardiovascular diseases
DASH: Dietary Approaches to Stop Hypertension
ECQ: Electrocardiogram
HDL: High-density lipoprotein
HTN: Hypertension
IPAQ: International Physical Activity Questionnaire
JNC: Joint National Committee
LDL: Low-density lipoprotein
PRECEDE: Predisposing, Reinforcing and Enabling Constructs in Educational Diagnosis and Evaluation
SMS: Short Message Service
WHO: World Health Organization
